### Sample size calculation

The sample size was calculated using the Power Analysis and Sample Size (PASS) (version 15.0, NCSS, LLC, East Kaysville, Utah, USA) based on a two-sided alpha of 0.05 and power of 0.8. According to previous literature [13], the ridge width changes in one site (at 1 mm apically from the top of the alveolar crest in central buccal) of ridge preservation group and natural healing group were 1.46 mm and -0.70 mm, respectively. And the SD were 3.54 mm and 2.28 mm. After the calculation, the minimal sample size was 30 extraction sites for each group. Considering 15% non-response rate, 35 extraction sites will be included in this study for each group. Totally, 70 extraction sites will be needed.

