**Methods:**

This research is designed as a two-group parallel randomized controlled trial. The total number of tooth extraction sites will be 70 after calculation with power analysis. Teeth will be randomly assigned to two groups with the test group conducting ridge preservation and the control group healing naturally. Periodontal examination, cone beam-computed tomography (CBCT) data, and stereolithographic (STL) files obtained by intraoral scanning will be collected through the follow-up period, and bone biopsy samples would be obtained during implant surgery. The primary outcomes are the vertical and horizontal change of alveolar ridge measured on CBCT images, soft tissue contour changes evaluated by superimposing the digital impressions, alterations of mucosa thickness (as measured by superimposing the CBCT data and STL files), histological features of implant sites and periodontal parameter changes. The secondary outcomes are patient-reported post-operative reaction and conditions of simultaneous bone graft or sinus lifting procedures during implantation.

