### Randomizing

A series of random numbers will be generated using Excel 2021 (Microsoft Corp., Redmond, WA, USA), written on letter paper and sealed in sequentially numbered, sealed, opaque envelopes. All the patients will be assigned to two groups by simple randomization with the rate of 1:1: the test group with alveolar ridge preservation, and the control group with natural healing. All the surgical procedures will be performed by an experienced clinician, and the other clinician will conduct the clinical examination for the patients. Another two members will take charge of intraoral scanning, assessing the radiological examinations and completing statistical analysis.

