### Statistical analysis

Statistical analysis will be performed using the SPSS 26.0 software package (SPSS Inc., Chicago, IL, USA). Descriptive data will be reported as mean ± standard deviations. A Shapiro–Wilk test will be applied to test for normal distribution of the sample for each variable. The paired t-test or Wilcoxon signed rank sum test when the data are not normally distributed will be applied to detect changes of soft and hard tissue before and 6 months after surgery. Independent samples t tests will be performed to compare parameter means between control and test groups. A non-parametric Mann–Whitney U test will be used if parameters are not normally distributed. Baseline characteristics of the patients who are lost to follow-up and completed this study will be compared. For the missing outcome data, K-means clustering method will be used for imputation. The level of significance was set at α = 0.05.

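### After the stated 15% loss, 35 sites per group give about 78% power for the planned t test, slightly below the stated 80%

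*Protocol article*

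**What the plan says.** The Sample size calculation section is "based on a two-sided alpha of 0.05 and power of 0.8". Its inputs come from one earlier study, at one measurement position. The ridge width changes in the "ridge preservation group and natural healing group were 1.46 mm and -0.70 mm, respectively". The spread is given next: "And the SD were 3.54 mm and 2.28 mm".

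It then concludes: "After the calculation, the minimal sample size was 30 extraction sites for each group". The enrolment figure follows: "Considering 15% non-response rate, 35 extraction sites will be included in this study for each group". The Abstract repeats the total: "The total number of tooth extraction sites will be 70 after calculation with power analysis".

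The section names the software but not the procedure within it (normal or t based), and gives no formula for the loss allowance.

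The between-group analysis is fixed in the Statistical analysis section: "Independent samples t tests will be performed to compare parameter means between control and test groups", with a Mann–Whitney test when data are not normally distributed.

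**The concern.** The section makes a joint claim: 30 sites per group is the least that gives 80% power, and enrolling 35 protects that number against 15% loss. Two small slips run in the same direction.

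- Enrolment of 35 with 15% loss leaves slightly fewer than 30.
- Thirty is not the minimum for the test the protocol plans to use.

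At stake is the accuracy of the stated power. This paragraph is the only justification for the sample size, and a reader who relies on it would credit the trial with slightly more power, after the loss it anticipates, than its own assumptions give.

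**Working it through.** **Inputs.** From Sample size calculation: two-sided alpha 0.05, power 0.80, difference 1.46 − (−0.70) = 2.16 mm, SDs 3.54 and 2.28 mm, 15% loss, 35 enrolled per group. From Randomizing: 1:1 allocation. From Statistical analysis: independent samples t test.

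**Step 1. Reproduce the 30.** With the normal approximation,

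n per group = (1.960 + 0.842)² × (3.54² + 2.28²) / 2.16²

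The variances sum to 12.5316 + 5.1984 = 17.73 and 2.16² = 4.6656. This gives n = 29.83, rounded up to 30. The protocol's figure is reproduced.

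**Step 2. Check the loss allowance.** 35 × 0.85 = 29.75, below 30. Conversely 30 / 0.85 = 35.29, and since a minimum must be rounded up, this gives 36 per group (72 in total).

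**Step 3. Power for the planned test.** For n evaluable sites per group, the noncentrality parameter is 2.16 / √(17.73 / n). The normal approximation takes power as Φ(noncentrality − 1.960). The t test uses the noncentral t distribution, with 2n − 2 degrees of freedom (pooled) or the Welch degrees of freedom.

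| Evaluable per group | Normal approximation | Pooled t | Welch t |
|---|---|---|---|
| 29 | 78.9% | 77.5% | 77.2% |
| 29.75 | 79.9% | 78.6% | 78.3% |
| 30 | 80.2% | 78.9% | 78.7% |
| 31 | 81.5% | 80.2% | 80.0% |
| 35 (no loss) | 85.9% | 84.9% | 84.7% |

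The t test first reaches 80% at 31 per group. Covering 15% loss then takes 31 / 0.85 = 36.47, so 37 per group (74 in total).

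If each site instead has an independent 15% chance of loss, Welch power averaged over the resulting group sizes is 78.1%, which agrees with the fixed-loss figures.

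**Step 4. Where the gap comes from.** On the normal approximation, which is the basis that reproduces the 30, power at 29.75 is 79.9%, so the loss allowance alone costs about 0.1 point against 80%. Moving from the normal approximation to the t test at 29.75 costs 79.9 − 78.6 = 1.3 points (pooled) or 79.9 − 78.3 = 1.6 points (Welch). Most of the shortfall is therefore normal versus t.

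**The case against.** The strongest case against the point is that it is too small to matter. The stated 30 is reproduced exactly by a standard method. The shortfall after loss is 80 − 78.6 = 1.4 to 80 − 78.3 = 1.7 points, or one to two sites per group. That is small beside the uncertainty in SDs taken from one source at one measurement position. A condensed article also need not name the software procedure. All of this stands, and it settles the severity. It does not make the stated power correct for the planned test after the stated loss.

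Two stronger readings are tempting, and the protocol does not support them.

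- A reader might infer that the allowance was added (30 × 1.15 = 34.5, rounded up to 35) where it should have been divided. The text gives no formula, and 30 / 0.85 = 35.29 rounded to the nearest whole number is also 35. How the figure arose cannot be told. What can be said is that 35 does not preserve 30 after 15% loss.
- A reader might infer that 35 sites per group are too few for 80% power in any case. They are not: if all 35 are analysed, power is about 85%. The figure near 78% holds only after the full assumed loss.

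It might also be argued that the planned imputation of missing outcomes restores the numbers. Imputed values add no independent observations, and the sample size section itself allows for lost sites by enrolling more.

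**Conclusion.** The point holds as a minor inaccuracy. On the protocol's own inputs, 80% power, 15% loss, 35 enrolled per group and a t test do not hold together. Power after the assumed loss is about 78%: 78.3–78.6% at the expected 29.75 sites per group, and 77.2–77.5% if whole-site rounding leaves 29 in each.

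This rests on the stated difference and SDs being right, normally distributed changes, independent sites, equal group sizes and 15% loss in both groups. It does not threaten the trial and does not call the design or the planned analysis into question.

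**What to change.** Keep 70 sites and correct the paragraph. It could read: with 35 sites enrolled per group and 15% loss, about 29–30 evaluable sites per group remain, giving about 78% power for the planned independent samples t test to detect 2.16 mm (SDs 3.54 and 2.28 mm, two-sided alpha 0.05); a full 80% would correspond to 31 evaluable, or 37 enrolled, per group. Stating whether the calculation was based on the normal or the t distribution would let a reader reproduce it.

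The cost is a change of wording and a stated power about 2 points lower. No extra participants or procedures are needed. Keeping the 80% claim instead would mean enrolling 74 sites, four more than planned.

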### Statistical analysis

Statistical analysis will be performed using the SPSS 26.0 software package (SPSS Inc., Chicago, IL, USA). Descriptive data will be reported as mean ± standard deviations. A Shapiro–Wilk test will be applied to test for normal distribution of the sample for each variable. The paired t-test or Wilcoxon signed rank sum test when the data are not normally distributed will be applied to detect changes of soft and hard tissue before and 6 months after surgery. Independent samples t tests will be performed to compare parameter means between control and test groups. A non-parametric Mann–Whitney U test will be used if parameters are not normally distributed. Baseline characteristics of the patients who are lost to follow-up and completed this study will be compared. For the missing outcome data, K-means clustering method will be used for imputation. The level of significance was set at α = 0.05.

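### The between-arm test is unadjusted and chosen variable by variable from a normality test, so pre-extraction measures are never covariates and the quantity tested depends on the data

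*Protocol article*

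**What the plan says.** The Statistical analysis section applies a Shapiro–Wilk test to each variable. It then states for the comparison of arms: "Independent samples t tests will be performed to compare parameter means between control and test groups". The alternative is: "A non-parametric Mann–Whitney U test will be used if parameters are not normally distributed". No covariate, model or unequal-variance version is named. Paired tests are listed separately, for change within the sample.

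The Sample size calculation section plans on means. The ridge-width changes "of ridge preservation group and natural healing group were 1.46 mm and -0.70 mm, respectively", "And the SD were 3.54 mm and 2.28 mm", and the calculation is "based on a two-sided alpha of 0.05 and power of 0.8". Its result is that "the minimal sample size was 30 extraction sites for each group", raised to 35 per group for losses.

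The Randomizing section says that patients will be "assigned to two groups by simple randomization with the rate of 1:1", with no blocks or strata.

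Under Outcome measures, CBCT 1, STL 1, probing depth (PD), gingival recession (GR) and width of keratinized tissue (WKT) are obtained before extraction. CBCT 2 is taken straight after the intervention in both groups. The section on superimposition takes the radiographic outcome as the change from CBCT 2 to CBCT 3, and compares later surface scans with STL 1.

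**The concern.** Three consequences follow from the stated analysis.

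- **Precision.** Sockets in stage III/IV periodontitis are likely to differ widely in starting defect. A change score uses the starting value with a fixed coefficient of one. A regression on the pre-extraction value estimates that coefficient and usually leaves less residual variance.
- **Target of the comparison.** The trial is sized to detect a mean difference of 2.16 mm. If Shapiro–Wilk rejects, the test no longer addresses a mean difference, and the choice can differ between outcomes within the same paper.
- **Error rate.** The planning SDs are unequal, and simple randomization does not guarantee equal arms. These are the conditions in which a pooled t-test can depart from its 5% level.

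At stake are power, a consistent effect measure across outcomes, and a dependable significance level.

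**Working it through.** **Inputs from the protocol.** Difference 1.46 − (−0.70) = 2.16 mm. SDs 3.54 mm (preservation) and 2.28 mm (control), so variances 12.53 and 5.20, ratio 2.41. Two-sided alpha 0.05, power 0.80, 30 per arm.

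**Inputs assumed.** The correlation r between the pre-extraction value and the outcome, shown over a range. The shape of the data under skew. Shapiro–Wilk run in each arm at 5%, with a switch if either arm rejects. Each site allocated independently.

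**1. The plan's own figure.** Average SD = √((12.53 + 5.20)/2) = 2.977. n = 2 × (2.977 × (1.960 + 0.842)/2.16)² = 29.8, so 30 per arm. The stated figure reproduces. The normal approximation gives power 80.2% at 30 per arm.

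**2. Gain from adjustment.** The residual SD is 2.977 × √(1 − r²).

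| r (assumed) | n per arm for 80% power | Power at 30 per arm |
|---|---|---|
| 0 | 30 | 80.2% |
| 0.2 | 29 | 81.8% |
| 0.3 | 28 | 83.8% |
| 0.5 | 23 | 90.0% |

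**3. Pooled t-test under unequal SDs.** At 25 preservation to 35 control sites:

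- Pooled variance: (24 × 12.53 + 34 × 5.20)/58 = 8.23.
- Squared standard error the test assumes: 8.23 × (1/25 + 1/35) = 0.565.
- True squared standard error: 12.53/25 + 5.20/35 = 0.650.
- The true standard error is √(0.650/0.565) = 1.07 times the assumed one, so the effective critical value falls from 2.00 to about 1.87. The size is then about 6.7%.

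Reversed, at 35:25, the two squared errors are 0.651 (assumed) and 0.566 (true), and the size falls to about 3.6%.

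Simulation with normal data (40,000 runs per split) agrees:

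| Preservation : control | Pooled t | Welch |
|---|---|---|
| 30:30 | 5.0% | 4.9% |
| 25:35 | 6.7% | 5.0% |
| 35:25 | 3.5% | 4.9% |

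Across all splits checked, Welch stays between 4.8% and 5.1%. A split of 35:25 or worse, in either direction, has probability 24.5% among 60 sites. Averaged over simple randomization, the pooled test has size 5.2% for 60 sites and 5.1% for 70.

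**4. The two-stage rule.** Rejection rate under equal means with the planning SDs, 5,000 runs per cell (error about 0.3 to 0.4 point), pooled t as the parametric option:

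| Data | Switch to Mann–Whitney at 30:30 | Rejection at 30:30 | Rejection at 25:35 |
|---|---|---|---|
| Normal | 10% | 5.3% | 6.8% |
| t with 5 df | 45% | 5.8% | 6.1% |
| Moderately skewed gamma | 69% | 7.6% | 8.7% |

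In the skewed case at 30:30, Mann–Whitney alone rejects 7.5% and the pooled t-test 5.2%. The excess arises because Mann–Whitney responds to differences in distribution when the means are equal. It is testing something other than the planned mean difference.

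**The case against.** The strongest reply has five parts.

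- **Baseline data are already used.** A reader might infer that the baseline scans are discarded. The protocol does not support that: CBCT 2 starts the radiographic change and STL 1 is the reference for later contours. What is absent is their use as covariates. This costs precision but does not bias a randomized comparison, since an unadjusted test already allows for chance imbalance.
- **The test is not shown to be mis-sized.** The article does not say whether the t-test is pooled or Welch. Welch holds its level, the pooled test holds it at the planned equal arms, and the average over simple randomization is close to 5%. A flat statement that the test has the wrong level would go too far. The distortion depends on the version used and the split obtained.
- **The gain rests on an unstated correlation.** This stands. At 0.2–0.3 the gain is only 2 to 4 points.
- **One adjusted model cannot serve every outcome.** This stands. Histology, mucosa thickness (first derived from CBCT 2 and the 2-week scan), implant PD and marginal bone loss have no pre-extraction value. Jaw is not listed as an analysis variable, although it follows from which molar is extracted.
- **An unseen analysis plan may supply the details.** This is fair for the t-test version. It does not answer the main point, because the article itself fixes the unadjusted tests and the normality switch.

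Nor should the paired tests be read as a comparison of arms. The article gives them a separate purpose.

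**Conclusion.** The point holds as a worthwhile improvement to a stated analysis choice, not as a fatal flaw. The article commits to unadjusted tests and lets a normality test decide, outcome by outcome, whether a mean difference or a rank shift is examined. That does not match a sample size built on a mean difference.

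The cost in power is between slight and material, depending on the correlation: from about 80% unadjusted to 82–84% (r = 0.2–0.3) or about 90% (r = 0.5) with adjustment. The cost in error rate is conditional. It is about 7.6% at 30:30 for the two-stage rule if the data are moderately skewed, and 6.7% or 3.5% for a pooled t-test at 25:35 or 35:25. With normal data and equal arms it is close to 5%. These figures rest on the planning SDs, on independent allocation of sites and, for the two-stage rule, on the assumed skew and way of applying Shapiro–Wilk.

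**What to change.** - **Outcomes with a pre-extraction measure** (ridge width and height from CBCT 1, contour from STL 1, WKT, and PD and GR of adjacent teeth): prespecify one linear model of the 6-month value or change on arm, the pre-extraction value and jaw. Use heteroscedasticity-robust standard errors and report the adjusted mean difference with its 95% confidence interval.
- **Outcomes without one** (histology, mucosa thickness, implant PD, marginal bone loss): use a Welch comparison with a 95% confidence interval, adjusted for jaw if wished.
- **Do not use CBCT 2 as a covariate.** It follows the intervention, and in the test group it follows grafting.
- **Drop the Shapiro–Wilk switch.** Keep Mann–Whitney as a sensitivity analysis.

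Most of this is a change of wording. The extra work is to define and read ridge dimensions on CBCT 1, which the article now uses only to assess anatomy, and to record jaw as an analysis variable. No new visit, scan or participant is needed.

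### K-means filling of missing outcomes, as worded, is single imputation that ignores its own uncertainty: it dilutes the effect or understates the standard error, depending on how clusters are formed

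*Protocol article*

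**What the plan says.** The Statistical analysis section of the protocol article gives one sentence on imputation: "For the missing outcome data, K-means clustering method will be used for imputation". It does not give the clustering features, the number of clusters, whether treatment arm enters the clustering, or how a value is taken from the cluster.

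For the between-group comparison it says "Independent samples t tests will be performed to compare parameter means between control and test groups", with a Mann–Whitney U test as the non-normal alternative. It describes no repeated imputation, pooling rule, variance adjustment or observed-data analysis. The only other step on missingness is a baseline comparison of those lost with those who completed.

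The Sample size calculation section shows how much missingness the plan expects: "Considering 15% non-response rate, 35 extraction sites will be included in this study for each group".

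**The concern.** K-means filling gives a missing site the central value of a cluster of similar sites. That value has no residual scatter and no allowance for having been estimated. An ordinary t test on the completed data then counts it as a real observation.

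The consequence depends on a detail the article does not settle:

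- **Clusters ignore arm.** Missing sites in both arms receive values averaged over test and control sites, so the arms are pulled together.
- **Clusters are formed within arm.** Missing sites receive values close to their own arm's mean. The SD shrinks while the full n is counted.

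At stake is either the size of the reported treatment effect or the honesty of its confidence interval and p-value. The rule covers missing outcome data without exception, so it reaches the outcomes that the Abstract lists as primary, including ridge change on CBCT. Naming the method is a stated choice, so this is not a detail left to a fuller document.

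**Working it through.** **Inputs, all from the article.** Two-sided alpha 0.05 and power 0.80 ("based on a two-sided alpha of 0.05 and power of 0.8"). Ridge width changes "of ridge preservation group and natural healing group were 1.46 mm and -0.70 mm, respectively", a difference of 1.46 − (−0.70) = 2.16 mm. "And the SD were 3.54 mm and 2.28 mm". Allocation 1:1 ("assigned to two groups by simple randomization with the rate of 1:1").

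**Step 1. Reproduce the plan's figure.** Root-mean-square SD = √((3.54² + 2.28²)/2) = 2.977 mm. The normal-approximation formula for two means gives 30 per group (power 80.2% at 30), matching "the minimal sample size was 30 extraction sites for each group". A t-based calculation gives 31, with about 79% power at 30. For non-response, 30 × 1.15 = 34.5 rounds up to the stated 35, while 30/0.85 gives 36. That difference is immaterial here. So 35 enrolled and 30 evaluable means about 5 missing per arm.

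**Step 2. Clusters ignore arm.** With non-predictive features, each filled value has the same expectation in both arms, so filled sites contribute no difference:

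expected estimate = 2.16 × 30/35 = 1.85 mm, a 14% dilution.

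The standard error shrinks by about the same factor, so the test statistic hardly changes. Simulation (35 per arm, 5 missing completely at random per arm, three clusters, 3000 runs per setting) gave:

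| Feature–outcome correlation | Mean estimate | Type I error | Power | Power, observed sites only |
|---|---|---|---|---|
| 0 | 1.87 mm | 5.0% | 80.1% | 80.6% |
| 0.3 | 1.85 mm | 4.6% | 78.6% | 78.7% |

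**Step 3. Clusters formed within arm.** With non-predictive features, take filled values at about the observed arm mean:

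- true SE = 2.977 × √(2/30) = 0.77 mm
- reported SE = 2.977 × √(29/34) × √(2/35) = 0.66 mm
- ratio = √(29/34 × 30/35) = 0.855, so the reported SE is about 15% too small.

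Type I error = 2 × (1 − Φ(c × 0.855)). With c = 1.96 this is 9.4%. With the t critical value on 68 degrees of freedom it is 8.8%, and 95% interval coverage is about 91%. In the simulation with correlation 0, type I error was 9.1%, against 5.2% for observed sites only, and the estimate was unbiased.

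**Step 4. Range over the amount missing.** The article gives no rate other than 15%, so 2 to 7 missing per arm is an assumption. The two middle columns are alternatives and do not add up.

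| Missing per arm (of 35) | Estimate if arm ignored | Type I error if within arm | SE ratio if within arm |
|---|---|---|---|
| 2 (5.7%) | 2.04 mm | 6.0% | 0.942 |
| 3 (8.6%) | 1.97 mm | 6.8% | 0.913 |
| 5 (14.3%) | 1.85 mm | 8.8% | 0.855 |
| 7 (20.0%) | 1.73 mm | 11.2% | 0.797 |

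**Step 5. Stronger features.** These are further simulations with 5 missing per arm, 1000 runs per setting, and Monte Carlo error of about 0.7 to 0.9 points on type I error.

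- Arm ignored, with features that themselves carry the treatment effect: 1.98 mm at correlation about 0.5 (8% dilution) and 2.07 mm at about 0.8 (4% dilution).
- Within arm: type I error 6.8 to 8.9% at 0.5 and 6.6 to 7.1% at 0.8. At 0.8 the reported SE was 0.69 mm against about 0.73 mm.

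**The case against.** The strongest reply is that one sentence in a journal article is being asked to bear a lot. It does not say that values are filled once, that filled values are analysed as if observed, or that the completed data feed the main analysis. A fuller document might describe donor draws or an observed-data analysis. This stands as a limit: those features are inferred from how K-means filling ordinarily works and from the tests named. It does not remove the point, because nothing in the text carries imputation uncertainty into the comparison.

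The size is also open to challenge. The 15% is a planning allowance, and the article schedules visits around routine maintenance to keep participants in. The scans at 2, 4 and 12 weeks may predict the 6-month outcome well. Both arguments stand, and Steps 4 and 5 show that the harms shrink accordingly.

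A reader might infer that the trial faces both a diluted effect and a nearly doubled false-positive rate. The documents do not support that. These are opposite ends of a range set by how clusters are formed. Mixed clustering could give some of each to a lesser degree, but pooled clustering does not inflate type I error and costs little power.

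A reader might also infer that biopsy results will be invented for sites that never receive an implant. The article says that biopsies are taken during implant placement. It does not say that histology at a site without an implant counts as missing outcome data, so this is an ambiguity to close.

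**Conclusion.** The point holds in a conditional form. As worded, the missing-data rule is a single imputation that ignores imputation uncertainty, and it is unsuitable for these comparisons. At the article's own allowance, with about 5 of 35 sites missing completely at random per arm and weakly predictive features, it has one of two effects:

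- the 2.16 mm difference is diluted to about 1.85 mm, with type I error near 5%; or
- the estimate is unbiased, but the SE is about 15% too small and type I error is about 9%.

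Across an assumed 2 to 7 missing per arm, the estimate falls to between 2.04 and 1.73 mm, or type I error lies between about 6% and 11%. Strongly predictive features reduce both harms. The figures treat sites as independent and take cluster means as the filled values.

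The rule also brings no gain. The sample size already allows for the loss, and under the same assumption the 30 observed sites per arm give an unbiased estimate, about 5% type I error and about 79% power. The mechanism is clear and the size moderate. Randomisation, data collection and sample size are unaffected. This should be fixed before analysis.

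**What to change.** Delete the K-means sentence from the Statistical analysis section and replace it with three statements.

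1. The main analysis uses observed outcomes in all randomised sites, by the planned between-group test or a likelihood-based model. Baseline adjustment is optional and is not needed to cure this defect.
2. A sensitivity analysis uses multiple imputation that includes treatment arm or is run separately by arm, with baseline CBCT measurements and earlier scans as predictors, combined by Rubin's rules. It is needed because an observed-data analysis is not protected if loss is selective, for example through removals under the Criteria for discontinuing section.
3. Histology is not treated as missing data to be imputed where no implant was placed and hence no biopsy was taken.

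The cost is analysis wording and a little programming. No new data or extra sites are needed. Compared with K-means filling, the confidence interval will be wider, which reflects the information actually collected.
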